**Study protocol not AMG/ not MPG**

**Summary**

In the light of demographic change the number of elders in road traffic increases. A variety of age related illnesses like dementia, cardiovascular or musculoskeletal diseases lead to impairments in driving related motoric but also cognitive functions like attention, visuospatial perception, reaction speed, decision-making ability and memory1-3. Studies could show that with increasing loss in functions mentioned above the risk of driving errors and accident frequency in road traffic also rises4,5. The assessment and counselling of patients in clinical practice with regard to driving safety is often associated with uncertainties also due to a lack of appropriate assessment tools6,7. Hence there is a distinct necessity of valid assessment instruments examining driving safety in elder patients.

In cooperation with Schuhfried (GmbH) from Mödling/Vienna and the Neuropsychological Department of the kbo-Inn-Salzach-Klinikum in Wasserburg/Inn, an economical, in clinical routine practice easily applicable assessment tool for driving safety will be conceptualized and validated on the basis of an on-road driving observation. For this purpose a sample of 40 healthy subjects and 40 subjects with mild cognitive impairment, all with a minimum age of 50 years, will be targeted.

At the beginning driving related cognitive functions like attention and executive functions will be comprehensively examined by means of established neuropsychological assessment instruments. Subsequently the on-road driving observation will be carried out, following a detailed protocol, in a driving instruction vehicle, with a licensed driving instructor. The assessment will be supplemented by driving specific anamnesis and questionnaires for self-assessment of driving safety. It should optimally be finished within one day. Construct validity, criterion-related validity as well as predictive value will be determined by means of the results from neuropsychological examination and the on-road assessment.

**1 Study title, version number, version date**Validation of a test set for assessment of driving safety of patients with cognitive impairment – „DRIVESC2“, version number: 1, version date: 06/04/2018

**2. Study direction, foundation**Principal investigator: PD Dr. rer. nat. [name]

Deputy principal investigator: [name]. med. [name]

Project coordination: [name], Psychologist (M.Sc.)

Foundation: SCHUHFRIED GmbH, 2340 Mödling, Austria

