Generally, single tests are not appropriate as indicators for driving performance, as they do not provide a comprehensive picture of the driving behaviour, have no or only a low predictive value and cannot achieve high sensitivity or specificity values30,31. Single tests merely provide indications of possible limitations of driving ability, but they cannot replace an on-road driving assessment32-34. Bennett & Hons (2016)35 stated that there is not an exclusive cognitive domain that reliably and validly represents fitness to drive17. It led to the conclusion that a comprehensive test battery consisting of test-combinations and multiple instruments, which survey different driving relevant cognitive functions, constitutes the best predictor for driving ability in elders with mild cognitive impairment30,36,37. Nonetheless the insufficient clarification of the validity criteria of these test-batteries has to be mentioned38, which should be accomplished by further instruments proximal and distal to the construct.
Furthermore there is a large gap between scientific evidence and clinical application, mainly impeded by the missing cut-off values of the majority of research results29. Only few studies eventually generated scores which allowed for a distinction between “fit to drive” and “unfit to drive”. Latest recommendations imply a classification accuracy of 80-90%39 to guarantee a consistently accurate prediction. In addition, in contrast to the previous dichotomization between safe and unsafe drivers, a trichotomization is suggested29 which should categorize drivers into “safe”, “uncertain” and “unsafe”, with the middle category entailing a more detailed assessment for accurate classification, e.g. with the aid of an on-road driving assessment. Developing this screening-tool highest importance should be ascribed to an efficient implementation in clinical practice. In other words, it should not be resource-intensive in terms of time and personnel, therefore suggesting a computer or tablet-based application.

The following research hypotheses can be deduced:

(1) We assume that mild cognitively impaired and healthy subjects will differ significantly regarding on-road driving performance.
(2) Among assessed cognitive domains we expect especially visuospatial performance, attention and executive functions to predict driving ability.

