(3) We expect the newly developed screening-tool to differentiate with high diagnostic accuracy between safe and unsafe drivers. The accuracy is estimated at a minimum of 80% and should exceed the accuracy of single neuropsychological tests.
(4) Besides it is expected that driving competence will additionally be predicted by factors like age, driving experience in years and mileage per year.

**4. Study aims**The aim of the study is to develop a screening-tool with high predictive validity regarding driving ability of cognitively impaired subjects. Construct validity and criterion-based validity should be tested through a standardized on-road assessment as well as cognitive neuropsychological tests proximal and distal to the construct. The high practical relevance results from the necessity of a screening-tool for driving ability which is economically, validly and reliably applicable, tablet-based and thus mobile usable in medical care practice to support a low-threshold, qualitatively valuable and safe assessment of fitness to drive and counselling with respect to mobility; not least to meet legal requirements on the practitioner’s and patient’s side in this field.

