The Mini-Mental-State-Examination (Folstein et al., 1975)40 is a screening tool applicable in clinical practice to assess cognitive deficits. It is considered to be a reliable tool for initial examination of patients, e.g. in the context of dementia, as well as follow-up monitoring. The Mini-Mental-State-Examination is carried out as an interview with the patient. On the basis of 9 set of tasks central cognitive domains are checked (temporal and local orientation, memory retention, attention, language and speech comprehension, reading, writing, drawing and calculating). The MMSE tasks comprise both answering of questions and performing simple actions.

b) Assessment of subjectively perceived complaints and symptoms
The PDQ (Perceived Deficits Questionnaire; Fehnel et al., 2016)41 is utilized for the self-rating of cognitive deficits and allows for statements about the subjectively in everyday life perceived cognitive complaints of the patients and an estimation of its appearance and frequency. The reference period covers the last seven days.
The Mini-Symptom-Checklist (Mini-SCL; Franke, 2017)42 measures the subjectively perceived complaints using predefined physical and psychic symptoms over the last seven days.

c) Assessment of driving competence (TQ-Drive) – duration ca. 7 minutes
This computer based questionnaire assesses driving anamnestic information such as driving experience in terms of mileage per year, personal importance of the motor vehicle, driving difficulties and avoidance behavior etc. It provides a general impression of the individual driving performance and potential traffic-relevant risk factors.

d) Test-Set Cognitive Functions Dementia (CFD) – duration ca. 60 minutes
The test-set CFD measures neuropsychological domains relevant for neurocognitive disorders (according to DSM-5). By means of the CFD test-set cognitive performances in neuropsychological domains like attention, verbal long-term memory, executive functions, expressive speech and perceptual motor functions can be assessed. Table 2 lists all individual tests used in the study in order of display including duration of implementation.

|  | Dimension | Test | Subtest | Duration |
| --- | --- | --- | --- | --- |
| 1 | Semantic fluency | WIWO | S1 | 3 |
| 2 | Lexical fluency | WIWO | S3 | 4 |
| 3 | Learning ability | AWLT  (Subtest 1) | S1 | 7 |
| 4 | Alertness (intrinsic-visual) | WAFA | S2 | 2 |
| 5 | Brief delayed recall | AWLT  (Subtest 2) | S1 | 2 |

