**10. Biometry**

Examining the correlation between driving behavior and cognitive assessment in patients with neurological disorders studies indicate an average to large effect sizes for the TMT (part A and B) and visuospatial tests such as the Judgement of Line Orientation Test16,17,22,45. Therefore it can be assumed that TMT-L (part A and B) and LAT can predict driving behavior with an average effect size. The calculated sample size of N = 80 results as follows: Supposing a power (1 – β) of 80% and an alpha-level of α = .05 a sample size of N = 77 is necessary to detect an average effect calculating a multiple regression with three predictors (TMT-L part A, part B and LAT). In case of early dropouts we calculate a sample size of N=80 for recruitment.
Data will be analysed by means of multivariate analyses of variances followed by post-hoc-t-tests as well as regression analyses evaluating the predictive validity of the individual tests.
Premises of statistical calculations – such as normal distribution of sample or homogeneity of variance – shall be checked upfront.

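### The tool is developed and validated on the same 80 people, so hypothesis 3 (at least 80% accuracy, better than single tests) would rest on optimistic apparent accuracy

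*Protocol*

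**What the plan says.** The Protocol describes development and validation as one exercise. The Summary states that the tool "will be conceptualized and validated on the basis of an on-road driving observation" and continues: "For this purpose a sample of 40 healthy subjects and 40 subjects with mild cognitive impairment". No second sample is named. Section 4 (Study aims) says "The aim of the study is to develop a screening-tool with high predictive validity regarding driving ability of cognitively impaired subjects" and goes on to test construct and criterion validity in the same study. The study title calls it a validation.

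Hypothesis 3, at the end of section 3, sets the standard: "The accuracy is estimated at a minimum of 80% and should exceed the accuracy of single neuropsychological tests". The background argues that the best predictor is "a comprehensive test battery consisting of test-combinations and multiple instruments, which survey different driving relevant cognitive functions". It does not list which tests will form the tool, how they will be weighted or where the cut-off will lie. The on-road result that counts as unsafe is not defined either.

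Section 10 (Biometry) plans MANOVA with follow-up t-tests and "regression analyses evaluating the predictive validity of the individual tests". Its sample size is for a regression with three predictors (TMT-L part A, TMT-L part B and LAT). It mentions no hold-out, cross-validation or other internal validation.

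**The concern.** When the same people supply the choice of tests, the weights, the cut-off and the accuracy estimate, the estimate partly measures how well the rule fits the chance features of that sample. The comparison in hypothesis 3 has the same weakness. A combination tuned to the data has more freedom than any one of its components, so it tends to look better there even when none of them carries information.

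The tool is meant for fitness-to-drive assessment and counselling in medical practice. An inflated accuracy and an unstable cut-off would carry over into that use and could misclassify drivers in either direction.

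**Working it through.** **1. The plan's own figure.** Section 10 gives N = 77 for three predictors, alpha 0.05, power 80% and an average effect. Taking average as f² = 0.15 (an assumption, since the protocol gives no number), the overall F test has 3 and N − 4 degrees of freedom and noncentrality 0.15 × N. At N = 77 this is 11.55 with 3 and 73 df. Power is 0.796 at 76, 0.802 at 77 and 0.819 at 80, so 77 reproduces. This calculation does not size hypothesis 3.

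**2. Candidate scores.** Section 8 says "Table 2 lists all individual tests used in the study in order of display including duration of implementation". Table 2 has 12 rows. Row 10 covers both delayed recall and recognition, which gives 13 main variables. Adding the Clock Drawing Test and LAT gives 15. Hypothesis 4 adds age, driving experience and mileage, giving 18.

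**3. Unsafe drivers.** The share in this sample is not stated. Section 3 quotes 13.6% failing an on-road test, for MCI only. I use a range (assumption). The accuracy from calling everyone safe is 1 − unsafe/80: 92.5% at 6 unsafe, 90% at 8, 80% at 16 and 50% at 40.

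**4. Pure noise, Youden cut-off.** Setting: N = 80, 15 scores with mutual correlation 0.3 and no relation to the outcome, linear discriminant score, everything evaluated in the same data.

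| Unsafe of 80 | Apparent AUC (true 0.50) | Balanced accuracy | Raw accuracy | Calling everyone safe |
|---|---|---|---|---|
| 6 | 0.91 | 88% | 84% | 92.5% |
| 8 | 0.87 | 84% | 82% | 90% |
| 40 | 0.75 | 72% | 72% | 50% |

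The combination beats the best single noise test in about 100% of runs on AUC and about 97% on balanced accuracy. On raw accuracy it wins in only about 29 to 36% of runs at 6 to 12 unsafe, rising to 97 to 98% at 40.

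**5. Pure noise, cut-off chosen to maximise raw accuracy.** Uncorrelated scores, 1,500 runs per setting. A correlation of 0.4 changes little.

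| Unsafe share | Calling everyone safe | 15 scores: mean accuracy | Runs reaching 80% | Beats best single | 3 scores: mean accuracy | Beats best single |
|---|---|---|---|---|---|---|
| 13.6% | 86% | 90% | 100% | 67% | 87% | 15% |
| 20% | 80% | 85% | 100% | 71% | 81% | 18% |
| 25% | 75% | 81% | 70% | 74% | 77% | 20% |
| 30% | 70% | 78% | 31% | 85% | 72% | 25% |
| 40% | 60% | 74% | 5% | 94% | 65% | 37% |
| 50% | 50% | 72% | 3% | 97% | 62% | 42% |

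With 18 scores, mean accuracy is about 1 to 2 points higher. If the combination instead uses a fixed 0.5 threshold while each single test keeps its best cut-off, the 15-score combination wins in 13% of runs at 13.6% unsafe and 73% at 50%.

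**6. Effect of internal validation.** With 10-fold cross-validation and the cut-off refitted in each fold (14 to 17 noise predictors, 40 noise samples per setting, so approximate), accuracy is 48–49% at 50% unsafe, 60% at 30%, 63–65% at 25% and 78% at 13.6%. The rates from calling everyone safe are 50%, 70%, 75% and 86%. The apparent performance disappears.

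**The case against.** **This belongs in the SAP.** Resampling details commonly do, and section 10 does not exclude internal validation. That part stands: the absence of a bootstrap recipe alone would not be a finding. But the use of one sample for both purposes, the claim to validate and the comparison in hypothesis 3 are in the Protocol's own text. A SAP could correct the optimism; it could not supply a new sample.

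**The fitted combination is not stated.** This also stands. The tests are established instruments, and the only regression specified has three predictors. That the tool is a data-fitted combination of many scores is a fair reading of sections 3 and 4, not an explicit plan. With three predictors the raw-accuracy advantage over the best single test occurs in a minority of runs.

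**A stronger reading is tempting:** that pure noise would reach about 80% accuracy and beat every single test, so that hypothesis 3 is met automatically. The documents do not support it.
- They fix neither the number of scores, nor the cut-off rule, nor the unsafe share.
- At 40 to 50% unsafe, 15 to 18 noise scores average about 72 to 75%.
- Where few drivers are unsafe, an accuracy of 82% at 8 unsafe is below the 90% from calling everyone safe. With a Youden cut-off the combination there usually loses to the best single test on raw accuracy.

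A reader might also set the null R² of 15 useless predictors, 15/79 = 0.19, against the powered R² of 0.15/1.15 = 0.13. That mixes a 15-predictor null with a three-predictor effect. The matching null value is 3/79 = 0.04, and the F test already allows for the number of predictors.

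**Conclusion.** The concern holds in a limited form. The Protocol sets hypothesis 3 without separating development from validation. If the tool is a combination fitted in these 80 people, its apparent performance and its comparison with single tests will be optimistic.

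With about 15 candidate scores the distortion is large and consistent on AUC and balanced accuracy. On raw accuracy, the measure hypothesis 3 names, it is variable: with cut-offs tuned in the data for both sides, a noise combination wins in about 30 to 98% of runs, depending on cut-off rule and unsafe share. It is much smaller with three predictors.

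Separately, raw accuracy alone cannot support hypothesis 3 when 20% or fewer of the drivers are unsafe, because the 80% mark is then reached without any test.

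These sizes rest on my count of 15 scores, an assumed range of 6 to 40 unsafe drivers, normally distributed noise scores and a linear discriminant. The direction of the bias does not depend on the exact values; the amount does.

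**What to change.** Add to section 10:

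- Hypothesis 3 is assessed on AUC, sensitivity, specificity and accuracy after bootstrap optimism correction or repeated cross-validation. Test selection, weighting and cut-off choice are repeated in every resample.
- Accuracy is shown next to the majority-class rate.
- The tool and the single tests are compared on the same out-of-sample predictions.
- The result is described as development with internal validation; the word validated is kept for a new sample.

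The cost is some extra programming and a reported accuracy below the apparent one. No further participants are needed.

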**3. Scientific background**

As a consequence of demographic change the number of elders in road traffic also increases. A variety of age related illnesses like dementia, cardiovascular or musculoskeletal diseases lead to impairments in motoric, sensorial and cognitive functions1-3,8, some of which, like attention and executive function, are closely related to driving safety9,10. Traffic participants have to process visual, acoustic and tactile information simultaneously, react adequately to them, be stressable, estimate distances as well as correctly interpret traffic signs and judge their own driving abilities properly8. Studies could show that with increasing loss of cognitive functionality the risk of driving errors and accident frequency in road traffic rises4,5, the driving safety as a consequence decreases12,13. Especially in dementia, for example Alzheimer’s disease – the most common form of dementia14, which inevitably sooner or later leads to a loss of driving ability15,16 – and furthermore has a progressive process, the risk is particularly high17. Also the insight into illness is degraded18,19, which is why the self-reliant examination of one’s own driving ability in the context of duty to precaution and self review required by law in Germany is not guaranteed20. Already in early stages of dementia impairment should be taken into account. Studies point out that even mild cognitive impairment (MCI) can be accompanied by a decrease of driving competence. MCI describes the prodromal symptoms of dementia diseases, which comprises cognitive impairments, however does not lead to notable constraints in functioning independently. A general driving ban or broad restrictions for seniors with MCI nevertheless is inappropriate, especially considering that impairments in driving relevant cognitive domains may not be distinct enough to justify the revocation of the driver licence. The guidelines for assessment of driving fitness do not generally exclude the possibility of participation on road traffic; yet 13,6% of MCI-patients don’t pass an on-road driving test22.

In modern societies mobility is essential regarding life quality and well-being. Consequently, in the interests of protecting patients and other road participants, the governmental revocation of driver licences must be critically weighed against values like preservation of self-confidence, freedom, self-responsibility and independence 23. Immobility often leads to social isolation, depression and a high level of stress for the family members caring for the patient24-28. That is why many older people are afraid of impending loss of their driver licence, and there is lack of knowledge concerning legal consequences neglecting their duty to precaution (“Vorsorgepflicht”, a German legal term describing ones duty to independently check up fulfilment of statutory requirements concerning driving ability). A possible starting point is a low-threshold, informal mobility counselling. In doing so licensed general practitioners, neurologists, psychiatrists etc. play a central role in this field, as they are often the first to be confronted with this topic and can sensitize the patient for it.

In clinical practice the issue of fitness to drive is associated with great uncertainties, both on practitioner’s and patient’s side6,7. Hence there is a distinct necessity of valid assessment instruments. Frequently brief-screenings such as the MMSE (Mini-Mental-State-Examination) are applied, which allow for a rough assessment of the cognitive status, although study results concerning the predictive value on driving safety are unsatisfying29. The results of neuropsychological tests, especially in domains like attention visuospatial perception, show moderate correlations with real on-road driving performance30,31. The observation of driving behaviour in an on road test, which is often considered a gold standard of investigation of the driving behaviour, cannot be provided usually due to its resource intensity.
Generally, single tests are not appropriate as indicators for driving performance, as they do not provide a comprehensive picture of the driving behaviour, have no or only a low predictive value and cannot achieve high sensitivity or specificity values30,31. Single tests merely provide indications of possible limitations of driving ability, but they cannot replace an on-road driving assessment32-34. Bennett & Hons (2016)35 stated that there is not an exclusive cognitive domain that reliably and validly represents fitness to drive17. It led to the conclusion that a comprehensive test battery consisting of test-combinations and multiple instruments, which survey different driving relevant cognitive functions, constitutes the best predictor for driving ability in elders with mild cognitive impairment30,36,37. Nonetheless the insufficient clarification of the validity criteria of these test-batteries has to be mentioned38, which should be accomplished by further instruments proximal and distal to the construct.
Furthermore there is a large gap between scientific evidence and clinical application, mainly impeded by the missing cut-off values of the majority of research results29. Only few studies eventually generated scores which allowed for a distinction between “fit to drive” and “unfit to drive”. Latest recommendations imply a classification accuracy of 80-90%39 to guarantee a consistently accurate prediction. In addition, in contrast to the previous dichotomization between safe and unsafe drivers, a trichotomization is suggested29 which should categorize drivers into “safe”, “uncertain” and “unsafe”, with the middle category entailing a more detailed assessment for accurate classification, e.g. with the aid of an on-road driving assessment. Developing this screening-tool highest importance should be ascribed to an efficient implementation in clinical practice. In other words, it should not be resource-intensive in terms of time and personnel, therefore suggesting a computer or tablet-based application.

The following research hypotheses can be deduced:

(1) We assume that mild cognitively impaired and healthy subjects will differ significantly regarding on-road driving performance.
(2) Among assessed cognitive domains we expect especially visuospatial performance, attention and executive functions to predict driving ability.
(3) We expect the newly developed screening-tool to differentiate with high diagnostic accuracy between safe and unsafe drivers. The accuracy is estimated at a minimum of 80% and should exceed the accuracy of single neuropsychological tests.
(4) Besides it is expected that driving competence will additionally be predicted by factors like age, driving experience in years and mileage per year.

**4. Study aims**The aim of the study is to develop a screening-tool with high predictive validity regarding driving ability of cognitively impaired subjects. Construct validity and criterion-based validity should be tested through a standardized on-road assessment as well as cognitive neuropsychological tests proximal and distal to the construct. The high practical relevance results from the necessity of a screening-tool for driving ability which is economically, validly and reliably applicable, tablet-based and thus mobile usable in medical care practice to support a low-threshold, qualitatively valuable and safe assessment of fitness to drive and counselling with respect to mobility; not least to meet legal requirements on the practitioner’s and patient’s side in this field.

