**6. Study design**
The study is designed as a monocentric, non-randomized cross-sectional-study at the kbo-Inn-Salzach-Klinikum Wasserburg/Inn. Cut-off-scores in the MMSE of < 27 and ≥ 18 allocate the participants to the experimental group of subjects with mild cognitive impairment. Subjects with a MMSE-score ≥ 27 will be assigned to the healthy control group. We expect the recruitment period to last about 24 months. Each of these groups undergo the same assessment procedure. Blinding is only possible for the driving instructor.

**7. Study population**Women and men with an age ≥ 50 years, who possess a valid driver licence and who are active drivers, i.e. have been driving regularly the last three month before participation, and speak fluently German language can participate in the study. Regarding possible use of medication an exact documentation and clarification of potential adverse effects on on-road driving should be carried out in the context of anamnesis. Subjects who are under dose escalation or medication shifts will be excluded. The consent ability has to be checked, doubts about it also lead to exclusion. 40 subjects with mild to moderate cognitive impairment and 40 healthy control subjects will be assessed, parallelized regarding age, education, sex, driving experience and mileage per year.

*General exclusion criteria for all participants (based on annex 4, statutory order of driving licences)*

- Current severe dementia (MMSE < 18)
- Current severe psychiatric, neurological or internistic disease
- Visual impairment (visual acuity worse than 60%; visual field <140°, double-vision, hemi-neglect)
- No fluent German in speech and writing

*Specific criteria for the experimental groups*Healthy subjects (CG):

- ≥ 50 years
- German as first language respectively German-speaking since early childhood
- MMSE ≥27
- No record of severe psychiatric or neurological diseases
- Currently no internistic disease
- Currently no radio- or chemotherapy for cancer treatment

Cognitively impaired subjects (EG):

- ≥ 50 years
- First language German respectively German-speaking since early childhood
- MMSE ≥18 and <27
- Patients from the following ICD-10 diagnosis groups
  - Organic, including symptomatic disorders (F00-F09), N=20
  - Affective disorders (F30-F39), N=10
  - Schizophrenia, schizotypal or delusional disorders (F20-F29) / Neurotic, stress-related and somatoform disorders (F40-F48), N=10

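### The sample size was derived for a regression and not for the safe/unsafe claim in hypothesis 3; few unsafe drivers may enter, and the 80% accuracy mark can be met without discrimination

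*Protocol*

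**What the plan says.** Hypothesis 3, at the end of Protocol section 3, is a classification claim: "We expect the newly developed screening-tool to differentiate with high diagnostic accuracy between safe and unsafe drivers". It puts the accuracy at 80% or more and adds that the tool should do better than single neuropsychological tests.

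Section 10 (Biometry) contains the only sample size calculation: "Supposing a power (1 – β) of 80% and an alpha-level of α = .05 a sample size of N = 77 is necessary" for an average effect, "calculating a multiple regression with three predictors (TMT-L part A, part B and LAT"). Three subjects are added for dropout, which gives 80.

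Enrolment is by MMSE score and not by driving status. Section 6 allocates subjects with MMSE 18 to 26 to the experimental group and those with 27 or more to the control group. Section 7 says: "40 subjects with mild to moderate cognitive impairment and 40 healthy control subjects will be assessed".

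Section 3 gives one on-road failure rate, taken from a cited meta-analysis: "13,6% of MCI-patients" fail. The on-road assessment (section 8, item g) rates every observation sequence on an 11-point scale with verbal categories.

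**The concern.** In a regression on a graded driving score, every subject contributes information. In a safe/unsafe classification, sensitivity is estimated only from the drivers who turn out to be unsafe. A total of 80 can therefore be enough for the first question and thin for the second. The protocol does not say that its calculation leaves hypothesis 3 uncovered.

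The second difficulty is the criterion. Overall accuracy depends on how common unsafe drivers are. If they are uncommon, a rule that never flags anyone scores well, so an accuracy of 80% can be reached by a tool that detects nobody.

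Section 4 intends the tool for medical practice, to support safe assessment of fitness to drive and to help meet legal requirements. Detecting unsafe drivers is the safety-relevant half of the claim. A conclusion of high diagnostic accuracy that rested mainly on correctly labelled safe drivers could mislead its users.

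**Working it through.** **1. The protocol's own figure.** Inputs from section 10: α = 0.05, power 80%, three predictors, average effect. No number is given for the effect, so I assume the conventional medium value f² = 0.15.

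- Omnibus F test: numerator df u = 3, denominator df v = N − 4, noncentrality λ = f² × N.
- At N = 77: λ = 0.15 × 77 = 11.55, v = 73, critical F = 2.73, power = 0.802.
- At N = 76 the power is 0.796, so 77 is the smallest N that reaches 80%. At N = 80 the power is 0.819.

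The figure reproduces. None of its inputs is a number of unsafe drivers, an accuracy, or a precision for sensitivity.

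**2. Expected number of unsafe drivers.** Formula: 40 × p(impaired) + 40 × p(control).

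| Failure rate, impaired | Failure rate, controls | Unsafe of 80 | Basis |
|---|---|---|---|
| 13.6% | 0% | 5.4 | rate from section 3 |
| 13.6% | 13.6% | 10.9 | same rate applied to controls |
| 30% | 0% | 12 | assumption |
| 40% | 0% | 16 | assumption |
| 50% | 0% | 20 | assumption |

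Chance adds spread. The binomial 95% range is 2 to 10 unsafe drivers for 40 subjects at 13.6%, and 5 to 17 for 80 subjects at 13.6%. With 40 subjects at 13.6%, the probability of three or fewer is 0.19.

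**3. Precision of sensitivity.** Exact (Clopper-Pearson) 95% intervals for an observed sensitivity near 80%:

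| Detected / unsafe | 95% interval |
|---|---|
| 4/5 | 28% to 99% |
| 9/11 | 48% to 98% |
| 16/20 | 56% to 94% |

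**4. What 80% accuracy shows.** A rule that calls every driver safe has accuracy 1 − (unsafe/80).

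- 5.4 unsafe: 1 − 5.44/80 = 93.2%.
- 10.9 unsafe: 1 − 10.88/80 = 86.4%.
- 12 unsafe: 1 − 12/80 = 85%.
- 16 unsafe: 1 − 16/80 = 80%, exactly the stated minimum.
- 20 unsafe: 1 − 20/80 = 75%, below it.

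Up to 16 unsafe drivers of 80, the absolute mark in hypothesis 3 is met by a rule with zero sensitivity.

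**The case against.** Several counter-arguments have force.

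- **The count is not fixed by the protocol.** The 13.6% is a literature rate for MCI. The experimental group is broader: MMSE 18 to 26, described in section 7 as mild to moderate impairment, with 20 organic and 20 other psychiatric diagnoses. Section 3 calls the risk in dementia particularly high. The figure of 11 needs healthy controls to fail at the MCI rate, which sits badly with hypothesis 1. No safe/unsafe threshold on the on-road scale is stated either. This stands, so 5 to 11 is conditional and must be shown beside the higher range.
- **Poor and good tools might still be distinguishable.** A reader might infer that a tool missing half of unsafe drivers could never be told apart from one that finds nearly all. That goes too far: 7/7 gives 59% to 100%, 10/11 gives 59% to 99.8%, and 13/14 gives 66% to 99.8%, all excluding 50%. The supportable statement is that the estimate would be imprecise.
- **No cut-off is promised.** A reader might infer that the trial will publish a cut-off or a three-way classification. Section 3 mentions missing cut-offs as a gap in earlier research and reports the three-way split as a suggestion from a cited source. Hypothesis 3 names only safe and unsafe drivers.
- **Hypothesis 3 sets no confidence-bound criterion.** It does not require the lower limit for accuracy to reach 80%, so the study should not be faulted for low power against that standard.
- **The regression fits other aims.** It suits hypothesis 2 and the aim of predictive validity in section 4, and sizing on one of several hypotheses is common in tool development. This stands, and it is why N need not change.
- **Hypothesis 3 also asks the tool to beat single tests.** A rule that flags nobody does not do that by itself. But if the comparison is also made on overall accuracy, it too is dominated by the safe drivers when unsafe ones are few.

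A SAP could specify the classification method. It would not alter the enrolment rule, the stated basis of N or the wording of hypothesis 3, all of which are in the protocol.

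**Conclusion.** The point holds in a limited form. The calculation is correct for the regression it describes, and it does not cover hypothesis 3. Enrolment by MMSE leaves the number of unsafe drivers to chance: about 5 to 11 at the protocol's own 13.6%, and about 12 to 20 if 30% to 50% of the impaired group fail and no control does. Across that whole range sensitivity stays imprecise; even 16/20 leaves an interval of 56% to 94%.

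The criterion is the firmer part of the finding. At 13.6%, labelling everyone safe is 86% to 93% accurate, and this rule meets the 80% mark up to 16 unsafe of 80. Hypothesis 3 as written could therefore support a conclusion of high diagnostic accuracy without any discrimination.

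This rests on three assumptions: the medium effect f² = 0.15 for reproducing N, the transfer of the MCI rate to this sample, and the illustrative higher rates. It does not show that N = 80 is wrong for the regression, nor that the classification must fail.

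**What to change.** Keep N = 80 and change the wording in two places.

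1. **Section 10:** state that the N = 77/80 calculation covers the three-predictor regression and not hypothesis 3.
2. **Hypothesis 3:** do not rest the claim on overall accuracy alone. Report sensitivity and specificity with exact 95% confidence intervals, together with the observed number of unsafe drivers.
3. **Hypothesis 3, supporting analysis:** add the concordance of the screening score with the graded on-road rating in all 80 drivers, compared with the best single test. This needs a one-line definition of how the 11-point sequence ratings combine into one value per driver. It supports the safe/unsafe question and does not replace it.
4. **Any cut-off from this sample:** describe it as provisional until it has been checked in a sample with enough unsafe drivers.

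No extra subjects or procedures are needed, because the 11-point ratings are already collected. The cost is a more modest claim: this study alone could not be said to deliver a validated cut-off.
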